## Abstract

**Background:**

Research in treatment of non-small cell lung cancer (NSCLC) has shown promising results with stereotactic ablative radiotherapy (SABR) of oligometastatic disease, wherein distant disease may be limited to one or a few distant organs by host factors. Traditionally, PET/CT has been used in detecting metastatic disease and avoiding futile surgical intervention, however, sensitivity and specificity is limited to only 81 and 79%, respectively. Mediastinal staging still identifies occult nodal disease in up to 20% of NSCLC patients initially thought to be operative candidates. Endobronchial ultrasound and transbronchial needle aspiration (EBUS-TBNA) is a minimally invasive tool for the staging and diagnosis of thoracic malignancy. When EBUS is combined with endoscopic ultrasound using the same bronchoscope (EUS-B), the diagnostic sensitivity and negative predictive value increase to 84 and 97%, respectively. Endoscopic staging in patients with advanced disease has never been studied, but may inform treatment if a curative SABR approach is being taken.

**Methods:**

This is a multi-centre, prospective, cohort study with two-stage design. In the first stage, 10 patients with oligometastatic NSCLC (lung tumour ± hilar/mediastinal lymphadenopathy) with up to 5 synchronous metastases will be enrolled An additional 19 patients will be enrolled in the second stage if rate of treatment change is greater than 10% in the first stage. Patients will be subject to EBUS or combined modality EBUS/EUS-B to assess bilateral lymph node stations using a N3 to N2 to N1 progression. Primary endpoint is defined as the rate of change to treatment plan including change from SABR to conventional dose radiation, change in mediastinal radiation field, and change from curative to palliative intent treatment.

**Discussion:**

If a curative approach with SABR for oligometastatic disease is being explored, invasive mediastinal staging may guide treatment and prognosis. This study will provide insight into the use of endoscopic mediastinal staging in determining changes in treatment plan of NSCLC. Results will inform the design of future phase II trials.

**Trial registration:**

Clinicaltrials.gov identifier NCT04852588. Date of registration: April 19, 2021. Protocol version: 1.1 on December 9, 2021.

## Background

Historically, the treatment of advanced non-small cell lung cancer (NSCLC) has focused on minimizing symptoms, and prolonging life [1]. The oligometastatic paradigm of cancer argues that distant disease is not widespread, but rather constrained by host anatomical and physiological factors, into one or a few distant organs [2, 3]. Recently, a phase II study evaluating aggressive treatment with stereotactic ablative radiotherapy (SABR) of oligometastatic disease of any cell type, has been associated with an improvement in overall survival compared to standard of care [4]. Phase III studies are currently enrolling patients to validate the results of this promising study.

Regional or distant metastasis in NSCLC are non-invasively assessed by computed tomography (CT), positron emission tomography (PET), integrated PET/CT, magnetic resonance imaging (MRI) and radionucleotide bone scans [5]. PET/CT has been particularly useful in detecting occult metastases and avoiding futile surgical resection [6]. However, a large meta-analysis of integrated PET/CT for mediastinal nodal involvement in NSCLC reported sensitivity and specificity of only 81 and 79%, respectively [7]. Despite widespread reliance on PET/CT, mediastinal staging still identifies occult nodal disease in up to 20% of NSCLC patients who are operative candidates [8, 9].

Endobronchial ultrasound and transbronchial needle aspiration (EBUS-TBNA) for invasive mediastinal staging is a powerful and minimally invasive tool used to stage and diagnose thoracic malignancies [5, 8–10]. When EBUS is combined with endoscopic ultrasound (EUS) using the same bronchoscope (EUS-B), the diagnostic sensitivity and negative predictive value increase to 84 and 97%, respectively [11].

Treatment paradigms in the past did not justify invasive mediastinal staging for patients with advanced disease, therefore the presence of occult mediastinal metastasis has never been elucidated. However, if a curative approach for oligometastatic disease is being explored, invasive mediastinal staging may inform treatment planning and guide prognosis.

## Methods/design

The purpose of this study is to evaluate the impact of invasive mediastinal staging for patients undergoing curative treatment for oligometastatic NSCLC.

This study is a prospective cohort study with two-stage design. Ten patients will be enrolled initially and analyzed in the first stage. If the rate of treatment change is greater than 10%, 19 additional patients will be enrolled to complete the second stage of the study. The study will be conducted at two academic centers in Ontario, Canada. (London Health Sciences Centre, Sunnybrook Health Sciences Centre). Data will be collected by investigators and clinical trial coordinators into a secured, prospective RedCap (The Vanderbilt University) database.

Ethics approval was obtained from the Ontario Cancer Research Ethics Board (#3575).

### Objectives

#### Primary endpoints

To determine the proportion of patients with changes to treatment intent and/or plan, defined as:Change from SABR to conventional dose radiationChange in mediastinal radiation fieldChange from curative intent to palliative intent treatment

#### Secondary endpoints

To determine the proportion of patients with occult mediastinal metastasisTo determine the sensitivity and specificity of radiologic staging of hilar/mediastinal lymph nodesTo identify the total number of lymph nodes sampled per procedureTo identify the nodal stations sampledTo determine the proportion of patients with complications from endoscopic staging

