#### Statistical analysis

Descriptive statistics will be generated for baseline patient, tumour and treatment characteristics for all patients enrolled in either the first stage (*n* = 10) or second stage (*n* = 19) of the Simon’s two-stage design. The primary endpoint of this study will be to determine the proportion of patients with changes to treatment intent and/or plan, which will be reported with a 95% confidence interval and compared against the null hypothesis of no changes (0%) using the binomial proportion test. The secondary endpoints of this study will include determining the proportion of patients with occult mediastinal metastasis, which will also be reported with a 95% confidence interval. The sensitivity, specificity and concordance (using univariable logistic regression) measuring the association between radiologic staging of hilar/mediastinal lymph nodes (predictor variable) and changes in treatment intent and/or plan (dependent variable) will be calculated. The total number of lymph nodes sampled per procedure and proportion sampled for each nodal station will be calculated for each patient. The proportion of patients with complications of endoscopic procedure will also be reported. All statistical analyses will be performed using SAS version 9.4 software (SAS Institute, Cary, NC, USA) with two-sided statistical testing at the 0.05 significance level.

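### Radiologic accuracy is set for hilar and mediastinal nodes together and analysed against treatment change, so no mediastinal accuracy against cytology is planned

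*Protocol article*

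**What the plan says.** The Secondary endpoints section of the protocol article aims to "determine the sensitivity and specificity of radiologic staging of hilar/mediastinal lymph" nodes. It names no separate mediastinal target, no reference standard and no unit of analysis.

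The Statistical analysis section describes sensitivity, specificity and concordance through a univariable logistic regression. The predictor is again "radiologic staging of hilar/mediastinal lymph nodes (predictor variable"), and the outcome side reads "changes in treatment intent and/or plan (dependent variable) will be calculated". Cytology does not appear in that sentence.

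The same section treats occult disease separately, for the mediastinum alone: the "proportion of patients with occult mediastinal metastasis, which will also be reported with a 95% confidence interval".

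The Background motivates the trial with mediastinal figures: "integrated PET/CT for mediastinal nodal involvement in NSCLC reported sensitivity and specificity of only 81 and 79%, respectively". The Methods/design section gives the purpose as evaluating invasive mediastinal staging.

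**The concern.** The trial asks whether endoscopy finds mediastinal disease that imaging misses. The accuracy endpoint that should quantify how well imaging reads the mediastinum is defined on a wider target and analysed against a different kind of outcome.

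Two things are at stake. First, the written analysis does not yield nodal accuracy: it asks whether imaging predicts a change of plan. Second, even with cytology as reference, one combined target can count a miss in the mediastinum as a success whenever a hilar node was seen. The accuracy result and the occult-disease result would then describe the same patient in opposite ways, with nothing in the article to tell the reader so.

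**Working it through.** **The plan's own figure.** The article gives no figure for this endpoint. Its only derivable figure is the two-stage design (10 then 19 patients, stop at 1 or fewer, reject at 6 or more of 29). An exact binomial calculation gives alpha 0.047 at 10% and power 0.805 at 30%, which agrees with the stated 0.05 and 80%. Nothing below changes it.

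**Step 1. How single patients are scored.** Occult is taken to mean mediastinal disease on cytology that imaging did not show in the mediastinum; the article does not spell this out.

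| Patient | Any node, against cytology | Mediastinum only, against cytology | Any node, against treatment change (as written) |
|---|---|---|---|
| A: hilar node only on imaging, malignant mediastinal cytology, plan changed | true positive | false negative | true positive |
| B: mediastinal node on imaging, malignant mediastinal cytology, plan unchanged | true positive | true positive | false positive |
| C: no node on imaging, malignant mediastinal cytology, plan changed | false negative | false negative | false negative |

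Patient A is also an occult mediastinal metastasis, so the two secondary endpoints part company there. Patient B shows why treatment change cannot serve as the reference for nodal accuracy: imaging that was right is scored as wrong. If scoring were per station, A's missed mediastinal station would be a false negative and the problem in the first column would disappear.

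**Step 2. Inputs for the size.** From the article: 29 patients at most (Sample size); 81% sensitivity and 79% specificity for the mediastinum (Background). Assumed, because the article gives no values:
- the same 81% and 79% hold for the hilar region, and errors in the two regions are independent;
- 25–40% of patients have N2/N3 disease (m), 15–20% have N1 only (n1), and the rest have none;
- a fraction f = 0.3 to 0.6 of N2/N3 patients also have hilar disease;
- scoring is per patient, any node positive, with cytology as the reference.

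**Step 3. Combined accuracy.**
- Specificity: 0.79 × 0.79 = 0.624.
- Sensitivity, one region diseased: 1 − 0.19 × 0.79 = 0.850.
- Sensitivity, both regions diseased: 1 − 0.19 × 0.19 = 0.964.
- Share of node-positive patients with both regions diseased: w = f·m/(m + n1). Lowest: 0.3 × 0.25/0.45 = 0.167. Highest: 0.6 × 0.40/0.55 = 0.436.
- Overall sensitivity, 0.850 + w × 0.114: 0.869 to 0.900.

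An imaging method with true mediastinal values of 81% and 79% would thus show about 87–90% and 62% on the combined target.

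**Step 4. Missed mediastinal disease that is scored as correct.** Given mediastinal disease missed on imaging, the chance of a positive hilar reading is (1 − f) × 0.21 + f × 0.81:
- f = 0.3: 0.147 + 0.243 = 0.39
- f = 0.6: 0.084 + 0.486 = 0.57

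Expected number of patients like A:
- low: 29 × 0.25 × 0.19 × 0.39 = 0.54
- high: 29 × 0.40 × 0.19 × 0.57 = 1.26

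If the trial stops at 10 patients, the same products give 0.19 to 0.43.

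**Step 5. Against the precision available.** The inputs imply 29 × 0.25 = 7 to 29 × 0.40 = 12 patients with mediastinal disease, so one reclassified patient moves sensitivity by 1/12 = 8 to 1/7 = 14 percentage points. As an illustration, 6 of 12 is 50% (exact 95% interval 21–79%) and 7 of 12 is 58% (28–85%). The shift is visible but lies well inside sampling error.

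**The case against.** The strongest reply is that the article writes no any-node rule. The combined term may name only the anatomical scope, as it does in the inclusion criteria, and scoring by station or by N category would also fit. Unit of analysis and positivity rules are often left to a fuller document. This stands in part: the misclassification of patient A is an inference. What weakens the reply is that the only analysis described uses a per-patient outcome with one predictor, and station-level scoring does not fit that model.

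It is also fair that the figures in steps 3 and 4 assume a cytology reference, so they do not describe the analysis as written. They show what would happen if the reference were corrected and the combined target kept.

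A reader might infer three stronger claims that the article does not support:
- **That occult disease would be hidden.** It would not: it is a separate endpoint, for the mediastinum, with its own interval, and patient A would be counted there. Two endpoints with different targets may differ without either being wrong.
- **That a planned comparison with 81% and 79% is invalid.** No such comparison is planned. Those figures are background for PET/CT, and eligibility also allows staging by CT with bone scan, so results might not match them even if split by region.
- **That hilar nodes do not belong in the analysis.** Stations 10 and 11 are sampled, and two of the three primary endpoint components (SABR to conventional dose, curative to palliative intent) are not confined to the mediastinum. Hilar accuracy is worth reporting, but beside the mediastinal result and not in place of it.

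**Conclusion.** The point holds in a limited form. Two parts are read directly from the text: the accuracy endpoint names both regions together with no mediastinal estimate, and the described analysis sets imaging against treatment change and not against cytology. The conflicting classification of a patient with hilar-only imaging is conditional on per-patient, any-node scoring.

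Under that scoring, a cytology reference and the assumed nodal mix, about one patient in 29 is affected (0.5 to 1.3). The assumptions of equal accuracy in both regions and independent errors are unverified, so the percentages show direction and order of size only. One descriptive secondary endpoint is concerned; the primary endpoint, the sample size and the stopping rule are not. It is worth changing because the change is cheap and gives an answer to the trial's own question.

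**What to change.** In the Secondary endpoints and Statistical analysis sections:
1. Define the main accuracy result as per-patient sensitivity and specificity of imaging for mediastinal nodes (N2/N3 malignant, yes or no), with endoscopic cytology as the reference and exact 95% confidence intervals.
2. Report hilar (N1) accuracy separately, and keep the combined any-node result as a further line if wanted.
3. State how contralateral hilar nodes are classed, since stations 10 and 11 are assessed on both sides.
4. State that hilar-only imaging with malignant mediastinal cytology is a mediastinal false negative, so that this endpoint agrees with the occult-metastasis endpoint.
5. If the association between imaging and treatment change is still of interest, keep it as a separate analysis and do not call it the accuracy of nodal staging.

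The cost is wording. Endoscopic assessment already runs level by level from N3 down to N1, and the stations sampled are already an endpoint, so no new procedure is needed. The downside is two small tables in place of one, with wide intervals: 10 of 12, for example, would be 83% with an exact 95% interval of 52–98%.

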### Patient selection

#### Inclusion criteria

Patients with oligometastatic NSCLC, including a primary lung tumour (± hilar/mediastinal adenopathy) with up to 5 synchronous metastasesRadical treatment intent to all sites is recommended at multi-disciplinary tumour board or by discussion by medical oncologist, radiation oncologist and/or surgeon.Age 18 years or olderGood performance status (Eastern Cooperative Oncology Group [ECOG] 0–1) with life-expectancy of at least 6 months as determined by enrolling physicianPatient has undergone staging investigations less than 3 months prior to registration.PET/CT and MRI brain (CT brain with contrast if contraindication to MRI) ORCT chest/abdomen, radionucleotide bone scan and MRI of brain (CT brain with contrast if contraindication to MRI)Pathologic confirmation of NSCLC

#### Exclusion criteria

Contraindication to EBUS and/or EUSUnable to provide consent for EBUS/EUSContraindication to chest radiotherapyPregnant or lactating women

### Intervention

#### Pre-treatment evaluation

Staging within 12 weeks prior to registration with either:Contrast-enhanced CT of the chest and abdomen, plus bone scan, plus MRI brain orWhole body PET/CT and MRI brain(note: CT brain allowed when MRI contraindicated)Histological confirmation of NSCLCPregnancy test for women of child-bearing potentialSigned Informed Consent prior to any study-specific activities

#### Endoscopic procedure

All procedures will be performed by one of the study investigators. Procedures will be performed in an endoscopy setting with moderate conscious sedation, without the use of general anesthesia. EBUS-TBNA will be used to assess bilateral lymph nodal stations in the following areas: 2, 3P, 4, 5, 7, 10, and 11. EBUS may be combined with EUS-B to enhance accessibility to stations 4 L, 7, 5, 8, and 9. The use of EUS-B is not mandatory. EBUS will always be performed initially to reduce risk of airway contamination. Nodal assessment will be done systematically using a N3 to N2 to N1 progression, and any lymph node > 5 mm in short axis or with malignant features (one or more of: round shape, hypoechoic, loss of central hilar structures, central necrosis) will be sampled a minimum of 3 times. A new needle will be obtained upon stage migration to avoid contamination. Rapid onsite cytological evaluation (ROSE) will not be used for assessing samples. All specimens will be placed into formalin fixative followed by a needle-rinse into cytolyte and formally reviewed by a cytopathologist.

#### Radiation therapy

Radiation treatment intent and dosage will be initially planned based on clinical imaging, prescribed by the treating radiation oncologist and/or based on discussion at a multi-disciplinary cancer conference. Following endoscopic staging, any changes to radiation treatment intent or dosage will be recorded.

### Adverse events

#### Definitions

Adverse Event (AE) or reaction is any unfavorable and unintended sign (including an abnormal laboratory finding), symptom, or disease temporally associated with the use of a medical treatment or procedure that may or may not be considered related to the medical treatment or procedure.

Serious Adverse Event (SAE) or reaction as defined in the ICH Guideline: Clinical Safety Data Management: Definitions and Standards for Expedited Reporting, E2A Section IIB includes any untoward medical occurrence that at any dose:Results in deathIs life-threatening (refers to an event in which the patient was at risk of death at the time of the event; it does not refer to an event which hypothetically might have caused death if it were more severe.)Results in persistent or significant disability/incapacity.Requires in-patient hospitalization or prolongation of existing hospitalization.Is a congenital anomaly/birth defect.

Important medical events that may not be immediately life-threatening or result in death or hospitalization may be considered a serious adverse event, when, based upon medical and scientific judgment, they may jeopardize the patient or may require intervention to prevent one of the other outcomes listed in the definition above.

Unexpected adverse reaction is one that the nature and severity is not consistent with the applicable product information (e.g., Investigator’s Brochure or Product Monograph, described in the REB/IRB approved research protocol or informed consent document), or occurs with more than expected frequency.

#### Causality (attribution)

An adverse event or reaction is considered related to the research intervention if there is a reasonable possibility that the reaction or event may have been caused by the research intervention (i.e. a causal relationship between the reaction and the research intervention cannot be ruled out by the investigator(s)). The relationship of an AE to the study treatment (causality) will be described using the following definitions:

Unrelated: Any adverse event for which there is evidence that an alternative etiology exists or for which no timely relationship exists to the administration of the study treatment and the adverse event does not follow any previously documented pattern. The adverse event, after careful consideration by the investigator, is clearly and incontrovertibly due to causes other than the intervention.

Unlikely: Any adverse event for which the time relationship between the study treatment and the event suggests that a causal relationship is unlikely and/or the event is more likely due to the subject’s clinical condition or other therapies concomitantly administered to the subject.

Possible: Any adverse event occurring in a timely manner after the administration of the study treatment that follows a known pattern to the intervention and for which no other explanation is known. The adverse event, after careful consideration by the investigator, is considered to be unlikely related but cannot be ruled out with certainty.

Probable: Any adverse event occurring in a timely manner after the administration of the study treatment that follows a known pattern to the intervention and for which no other explanation is known. The adverse event, after careful consideration by the investigator, is believed with a high degree of certainty to be related to the intervention.

Definitely Related: Any adverse event occurring within a timely manner after administration of the study treatment that is a known sequela of the intervention and follows a previously documented pattern but for which no other explanation is known. The adverse event is believed by the investigator to be incontrovertibly related to the intervention.

#### Severity

The severity of adverse events will be evaluated using the Common Terminology Criteria for Adverse Events (CTCAE) v5.0 grading scale (see (http://ctep.cancer.gov).

Grade 1: Mild.

Grade 2: Moderate.

Grade 3: Severe.

Grade 4: Life-threatening or disabling.

Grade 5: Death.

Note: The term “severe” is a measure of intensity: thus a severe adverse event is not necessarily serious. For example, nausea of several hours’ duration may be rated as severe, but may not be clinically serious.

#### Immediately reportable adverse events

Any grade 4 or 5 adverse reaction that is definitely, probably, or possibly the result of protocol treatment must be verbally reported to the Principal Investigator and Central Office within 24 h of discovery.

All serious, unexpected adverse events or reactions regardless of causality must be reported to the Central Office and the Principal Investigator within 24 h of discovery. All unexpected SAEs must be reported to the local research ethics board according to local policies.

